### Sample

The sample will consist of health care professionals, patients with high risk for CVD or established CVD and their alters.

#### **
*Health care professionals*
**

We will include all health care professionals working in general practices participating in the RCT and who are involved in patient care (typically, general practitioners, practice nurses, and practice assistants). Based on power calculations in the RCT, 30 practices are planned to be included.

#### **
*Patients*
**

Eligible patients are adults aged 18 or older, with high risk of CVD or established CVD and who are capable of providing informed consent [30]. Patients with high risk for CVD have a risk score of 20% or higher of 10-years-morbidity and mortality due to CVD. International Classification of Primary care (ICPC) codes will be used to extract eligible patients from medical records. Exclusion criteria are: diabetes mellitus, pregnancy and lactation, terminal illness, cognitive impairments, and poor language skills. Per practice we plan to include 15 patients with established CVD and 15 at high risk.

#### **
*Alters*
**

*Alters of health care professionals* will comprise individuals with whom information on CVRM is exchanged but who are not part of the general practices’ network, as well as opinion leaders from outside general practices. We aim to include all alters of health care professionals.

*Alters of patients* include key individuals for information exchange, which most likely will be spouses or children of patients. We aim to include up to four persons considered to be important for dealing with patients’ condition or disease as indicated by the included patients in our measurements.

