**Health outcomes** Health outcomes will consist of SBP, cholesterol, and risk score. Thresholds for desired treatment values for SBP and cholesterol may differ for patients at risk, with established CVD, patients of certain ages, and according to individual targets set in agreement with treating health professionals and will be analyzed accordingly. Risk scores, only applicable to patients without established CVD, will be calculated using prevailing risk estimation tables [36]. The following parameters will be used in the calculation: age, gender, smoking status, systolic blood pressure (SBP) and total cholesterol/HDL-cholesterol ratio. The Epa Cardio abstraction tool [31] for medical audit will be used for abstracting these health outcomes.

#### **
*Other measures on patients will include*
**

##### 

**Descriptive variables** Descriptive measures will include age, sex, ethnicity, marital status, educational level, and social economic status (SES). For data collection we will use a questionnaire containing items from the Epa cardio abstraction tool [32].

##### 

**Information items for constructing social networks** For constructing and measuring social networks, patients are asked to indicate on a network roster from which persons they have received information on 1) medical treatment, 2) handling their condition or disease, and 3) practical help. We will provide a specifically developed and personalized roster questionnaire with names and disciplines of health professionals from their general practices (see Additional file 3: Appendix 3a). Patients are offered the possibility to add names of other persons (healthcare professionals/people in personal circle) they have received information from.

Alters are asked to indicate on a network roster to which persons they have provided information on 1) medical treatment, 2) handling their condition or disease, and 3) practical help using a specifically developed and personalized roster questionnaire (see Additional file 3: Appendix 3b).

##### 

**Frequency of contact** For measuring frequency of contact, patients will be asked to indicate how often they have received information from persons who have provided information in the last year. Similarly, alters will be asked how often they have provided information.

##### 

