In the analyses of self-management and health outcomes in patients, several multivariate logistic regression models will be estimated. For self-management, separate models will be estimated on physical activity, diet, and smoking. For health outcomes, separate models will be estimated on SBP, cholesterol, and risk score. Models will include four network characteristics as predictors: number of alters with favorable health behaviors, who are also connected among each other, number of alters with depressive symptoms, and number of alters who can provide CVRM-related information. The regression models will be controlled for trial arm (intervention vs control group), patient group (high risk or established CVD), and several personal characteristics: age, sex, ethnicity, marital status, SES, patient activation, therapy adherence, and depressive symptoms.

Two approaches will be used to investigate effects of social network characteristics on change in professional performance of practice nurses and self-management and health outcomes of patients after the intervention period at six month follow-up. First, follow-up outcomes measures will be treated as dependent variables. We will estimate similar models as described above and include baseline measures of outcomes of interest as predictors. Second, we will consider change as the difference between the baseline- and follow-up measures of the diverse outcomes of interest. Ordinal logistic regression models will be estimated, with change represented in three categories; a shift from inadequate to adequate outcomes, no change, and shift from adequate to inadequate outcomes.

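### SBP, cholesterol and risk score are analysed only as categories; adding baseline-adjusted continuous models and fixing each patient's threshold at baseline is a cheap improvement

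*Protocol article*

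**What the plan says.** The Health outcomes paragraph (Primary outcomes for patients) lists SBP, cholesterol and a calculated risk score, to be abstracted from medical records. All three are numerical.

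- **Model type.** Statistical analyses states for self-management and health outcomes that "several multivariate logistic regression models will be estimated", and then: "For health outcomes, separate models will be estimated on SBP, cholesterol, and risk score".
- **Change, first approach.** The follow-up outcome is the dependent variable: "We will estimate similar models as described above and include baseline measures of outcomes of interest as predictors". The models remain logistic.
- **Change, second approach.** Ordinal logistic regression, "with change represented in three categories; a shift from inadequate to adequate outcomes, no change, and shift from adequate to inadequate outcomes".
- **Thresholds.** "Thresholds for desired treatment values for SBP and cholesterol may differ for patients at risk, with established CVD, patients of certain ages", and also "according to individual targets set in agreement with treating health professionals and will be analyzed accordingly". The sentence concerns SBP and cholesterol only. It does not say whether the threshold at follow-up is the one that applied at baseline.
- **Risk score.** "Risk scores, only applicable to patients without established CVD, will be calculated using prevailing risk estimation tables".

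The hypotheses on professionals and on patients (Key hypotheses) are worded as reaching CVRM targets.

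**The concern.** There are two separate issues.

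**Information.** Reducing a continuous measurement to on or off target treats a patient just above the threshold like one far above it. Associations with network characteristics are then estimated less precisely than the abstracted data allow. The loss is greater for change, because most patients stay in the same category and fall into the middle group however far their values moved. Change is one of the four research aims and is called a main interest for patients.

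**A threshold that can move.** Where an individual target for SBP or cholesterol is revised between the visits, a patient can switch category with an unchanged measurement. The shift outcome then mixes change in the risk factor with change in the target.

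**Working it through.** **1. The plan's own calculation.** The only sample size in the article is 338 patients, for response rates of 50% and 65%. With the arcsine formula, h = 2·asin(√0.65) − 2·asin(√0.50) = 0.3047, and total N = 4 × ((1.960 + 0.842)/0.3047)² = 338. It reproduces, but it concerns invitation methods and says nothing about SBP, cholesterol or risk score.

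**2. Loss from the binary cut.** For a normal outcome with a share p on target, the efficiency relative to the continuous analysis is E = φ(z_p)² / [p(1−p)].

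- p = 0.5: 0.3989²/0.25 = 0.637
- p = 0.7: 0.3477²/0.21 = 0.576
- p = 0.8: 0.2800²/0.16 = 0.490

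The formula is symmetric, so p = 0.2 gives the same result as p = 0.8. The article plans 900 patients in 30 practices, 15 per practice with established CVD and 15 at high risk. The risk score therefore applies to 30 × 15 = 450. Suppose a continuous analysis of all 900 has 80% power. The binary analysis then has power Φ(2.802·√E − 1.960).

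| Share on target (assumed) | E | Loss | Equivalent N of 900 | Equivalent N of 450 | Power |
|---|---|---|---|---|---|
| 50% | 0.637 | 36% | 573 | 286 | 0.61 |
| 70% | 0.576 | 42% | 518 | 259 | 0.57 |
| 80% | 0.490 | 51% | 441 | 220 | 0.50 |
| 90% | 0.342 | 66% | 308 | 154 | 0.37 |

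**3. Loss in the change analyses.** This was simulated with n = 900, 2,000 runs, a normal outcome, baseline/follow-up correlation 0.5 or 0.7, and 50% or 70% on target. The effect was set so that a linear model of the follow-up value, adjusted for the continuous baseline value, has 80% power.

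| Correlation, share on target | Power, logistic with binary baseline | Power, ordinal shift | Loss, logistic | Loss, ordinal |
|---|---|---|---|---|
| 0.5, 50% | 0.56 | 0.41 | 46% | 64% |
| 0.5, 70% | 0.52 | 0.37 | 51% | 68% |
| 0.7, 50% | 0.47 | 0.37 | 56% | 68% |
| 0.7, 70% | 0.40 | 0.31 | 62% | 72% |

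The logistic column assumes that the baseline measure enters as on or off target. The article does not say in which form it enters.

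**4. Effect of revised targets alone.** The inputs are illustrative assumptions, not figures from the article and not a proposed target: SBP mean 140 and SD 15 or 20 at both visits, correlation 0.6, threshold 140, relaxed by 10 mmHg at follow-up in a fraction q of patients, and no change in SBP. The share on target at follow-up is 0.50 + q × [Φ(10/SD) − 0.50].

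- SD 15: Φ(0.667) = 0.748, so q = 0.1 gives 0.525 and q = 0.3 gives 0.574.
- SD 20: Φ(0.5) = 0.691, so q = 0.1 gives 0.519 and q = 0.3 gives 0.557.

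In simulation, shifts onto target rise from about 15% to 16-19%, and shifts off target fall from about 15% to 12-14%.

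None of steps 2-4 models clustering by practice.

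**The case against.** The best defence is that target attainment is the hypothesis. A model of mean SBP answers a different question, particularly when targets differ by patient group and age. The aims are exploratory and no power is claimed for these models. This stands, and it is why the binary analysis should stay. It does not justify having no continuous analysis beside it.

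The first change approach already adjusts for baseline. That also stands: change is not analysed by the three-category shift alone. If the baseline enters in continuous form, the logistic losses in step 3 are too high for that approach. Its outcome is still binary.

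A reader might infer more than the article supports in four respects:

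- **That professionals' target-setting biases the results.** The health-outcome models are specified with predictors describing the patient's own network. Professional networks are linked to targets in the hypotheses on professionals and in the outcomes section for professionals, but no such model is set out in detail. Nothing shows that target revision follows network characteristics. Without that link it adds noise.
- **That individual targets also govern the risk score.** The threshold sentence names only SBP and cholesterol.
- **That the risk-score model has no variation at baseline,** because "Patients with high risk for CVD have a risk score of 20% or higher of 10-years-morbidity and mortality due to CVD". The article does not propose a cut at 20%. Patients are extracted by diagnosis codes, while the analysed score is calculated from abstracted values, so the two need not agree. An article may leave the cut-off to the full protocol or analysis plan.
- **That the number of patients analysed can be taken as 50-65% of 900.** Those rates are assumptions for the invitation comparison, and the risk score in any case covers only half of the planned sample.

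**Conclusion.** The point holds as a cheap improvement. The article fixes categorical analyses for three numerical outcomes, both cross-sectionally and for change, and plans no continuous one.

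The size is conditional. With a normal outcome and 20-80% on target, the binary cut costs about 36-51% of the information. The article gives neither condition, and normality is least safe for a risk score in patients selected for high risk. The three-category shift costs more: 64-72% under the simulated conditions.

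The movable threshold is a gap for SBP and cholesterol only. Under the illustrative assumptions, revision alone moves the share on target by about 2 to 7 percentage points with unchanged SBP. This is noise unless revision is related to network characteristics, which the article does not show.

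**What to change.** 1. Keep target attainment as the analysis of the stated hypothesis.
2. Add linear models for SBP, cholesterol and risk score as continuous outcomes, with the same network predictors and control variables, and with clustering by practice accounted for (for example by a random effect). Restrict the risk-score model to patients without established CVD, and drop patient group as a covariate there.
3. In the follow-up versions, adjust for the continuous baseline value.
4. In the shift analysis of SBP and cholesterol, state that the threshold in force at baseline defines adequate at both measurements. This is a rule for the analysis only and leaves the targets used in care untouched.

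The measurements are already to be abstracted. The individual target at baseline must be recorded where one exists, which the planned analysis already needs. The cost is six secondary models (three outcomes, at baseline and at follow-up) with their coefficients to report, labelled as secondary so that they do not compete with the target-attainment results.

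### The risk score is analysed as adequate or inadequate only in patients included because that score is 20% or higher, so the baseline outcome may not vary at all; a continuous analysis avoids this

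*Protocol article*

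**What the plan says.** Three parts of the protocol article bear on this point.

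- **Selection** (Sample, Patients): "Patients with high risk for CVD have a risk score of 20% or higher of 10-years-morbidity and mortality due to CVD". The other eligible group has established disease. Patients are found through diagnosis codes: "codes will be used to extract eligible patients from medical records". The planned numbers are: "Per practice we plan to include 15 patients with established CVD and 15 at high risk".
- **Outcome** (Primary outcomes for patients, Health outcomes): "Risk scores, only applicable to patients without established CVD, will be calculated using prevailing risk estimation tables". The paragraph discusses target values for the other two health outcomes ("Thresholds for desired treatment values for SBP and cholesterol may differ for patients at risk") but gives no cut-off for the risk score.
- **Models** (Statistical analyses): patient outcomes are analysed by logistic regression, and "For health outcomes, separate models will be estimated on SBP, cholesterol, and risk score". At follow-up, the same models are run with the baseline outcome added as a predictor. A second approach is an ordinal logistic model with three categories: inadequate to adequate, no change, and adequate to inadequate. One covariate list serves all patient models and includes "patient group (high risk or established CVD").

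**The concern.** Logistic and ordinal-shift models need an outcome that takes both values. Here the outcome is cut into two in a group chosen by a threshold on the same variable. Depending on where the cut lies and which measurement counts as baseline, the dichotomy may have no variation at baseline, or it may separate patients who lie just either side of the inclusion value.

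The risk score is one of three named health outcomes, and the article lists effects on health outcomes among its main outcomes for patients. The baseline analysis of this score might be impossible, and the change analysis might carry less information than the collected data allow.

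**Working it through.** **Number of patients.** The article plans 15 high-risk patients and 15 with established disease in each of 30 practices.

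- All patients: (15 + 15) x 30 = 900, which matches the article's total.
- Patients with a risk score: 15 x 30 = 450, before any non-response or missing values.

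The article's own sample size of 338 concerns response rates to the invitation and has no bearing on these models.

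**Reading 1: cut-off c at or below 20%, baseline = qualifying score.** Let R0 and R1 be the baseline and follow-up scores, with Y = 1 (adequate) if R < c.

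- Inclusion requires R0 >= 20% >= c, so Y0 = 0 for everyone: 0 of 450 adequate.
- Baseline logistic model: the observed odds are 0/450, the log odds are minus infinity, and no coefficient can be estimated.
- Follow-up model: a dichotomised Y0 is constant and cannot be separated from the intercept.
- Change model: Y1 - Y0 can only be 0 or 1, so the adequate-to-inadequate category is empty. The two remaining categories are simply Y1, so the second approach to change repeats the first.

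**Reading 2: cut-off above 20%, baseline = qualifying score.** The article gives no distribution, so this is an illustration under assumptions: log-normal score in the source population, median 20%, log SD 0.5, reliability 0.8, no true change. Share adequate at baseline = P(R0 < c | R0 >= 20%) = 2 x [Phi(ln(c/20)/0.5) - 0.5].

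| Cut-off | Adequate at baseline | Shift to adequate | Shift to inadequate |
|---|---|---|---|
| 15% | 0% | 4.9% | 0% |
| 20% | 0% | 20.5% | 0% |
| 25% | 34.5% (about 155 of 450) | 18.4% | 11.4% |
| 30% | 58.2% (about 262 of 450) | 14.6% | 12.3% |

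At a 20% cut-off with median 20%, the shift can be checked by formula: arccos(0.8)/pi = 0.205.

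The models can be fitted at 25% or 30%, but adequate then includes patients whom the Sample section defines as high risk.

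**Reading 3: baseline re-measured after selection, cut-off 20%.** The same kind of simulation, with log SD 0.4 or 0.6 and reliability 0.7 to 0.9 (all assumed) and no true change:

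| Assumed median | Below 20% when measured again | If that is baseline: later shifts, each way |
|---|---|---|
| 12% | 25% to 53% | about 11% to 17% |
| 20% | 14% to 25% | about 7% to 13% |
| 25% | 9% to 18% | about 5% to 10% |

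Here 9% to 53% (about 38 to 239 of 450) are already adequate at baseline, and later shifts are equal in both directions. If the qualifying score is itself the baseline, the middle column gives instead the share that would cross below 20% at follow-up without any real change, all in one direction.

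**Covariate.** Under every reading, all patients in the risk-score model belong to the high-risk group, so patient group takes a single value and its coefficient cannot be estimated.

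**The case against.** The strongest reply is that the failure is conditional. The article fixes neither the cut-off nor the measurement that serves as baseline, and a condensed article may leave both to a fuller plan. Patients are extracted by diagnosis code, while the outcome score is calculated from abstracted values, so the two may differ. This stands. A reader might infer that there are no adequate patients at baseline and that change can run one way only. The documents do not support that as a flat statement, because it holds only under Reading 1. Even there, the follow-up logistic model without the constant predictor can still be estimated.

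A reader might also infer that follow-up change is dominated by regression to the mean. That is not supported either. The article gives no spread, reliability or expected true change, and the illustrative range is very wide. With a re-measured baseline, the net regression has largely happened before baseline. Regression to the mean also does not by itself create an association with network characteristics; it adds noise and one-sided shifts.

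Adjusting for age and sex, which enter the score, might look like a mistake. It is not: it removes variation that patients cannot modify.

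Finally, the aims are exploratory, this is one of six patient outcomes, and a constant covariate biases nothing. All of this limits the stakes. What remains is that the article itself states the model class, the change categories and the covariates, and these do not fit the population it states.

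**Conclusion.** The point holds in conditional form. Three things follow from the text alone: the risk score is dichotomised in a group selected on that score, at most 450 of 900 patients contribute, and patient group is constant in the model.

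A baseline with 0 of 450 adequate follows only if the cut-off is 20% or lower and the qualifying score is the baseline; the article states neither condition. Under the other readings the models can be fitted, but they discard information by cutting the score at or near its selection value, and some shifts may reflect regression to the mean. The percentages for those readings rest on assumed distributions and show only that the answer depends on choices the article leaves open. The analysis of this outcome should be changed, but the rest of the patient analysis is not undermined.

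**What to change.** For the risk score only, replace the logistic and ordinal-change models by linear models of the log score in the high-risk group:

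- **Baseline:** log R0 on the four network characteristics and the personal covariates, with a random intercept for practice or another allowance for clustering.
- **Follow-up:** log R1 on the same terms plus log R0 and trial arm, with the same allowance for clustering.

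Drop patient group from these models; age and sex may stay. State n of about 450, and say which measurement is the baseline and how it relates to the qualifying score. If a dichotomised version is kept as a supporting analysis, its cut-off should be stated and reconciled with the inclusion threshold. The SBP and cholesterol models are not affected.

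The cost is a change of wording, since all inputs to the score are already collected. Results would be reported as a ratio of risk scores (or a difference on the log scale) rather than as odds of being adequate. If the qualifying score is the baseline, its lower end is still cut off by inclusion, so the baseline model describes differences within the high-risk group only.

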### Theoretical background

The potential relevance of social networks for health outcomes is illustrated by a number of studies, which suggested that health-related behaviors are not randomly spread in a population but associated with social network structures [12-14]. This has led to the notion of ‘contagion processes’ in social networks, which seem to apply to a range of items, including infections, information, and behaviors. The underlying mechanisms of contagion patterns are heterogeneous, depending on the item of interest. For spread of information and behaviours, psychological mechanisms such as imitation of successful behaviours, role modelling, social comparison and selection of contacts can be drivers of contagion.

Contagion processes can be either simple or complex. In simple contagion processes, a single encounter has direct consequences. If applied to the transfer of information, the assumption is that access to information is the main enabler of uptake. Given the wide range of available information sources in health care, including many on the world wide web, and resulting information overload for both health professionals and patients, simple contagion may currently be rare. In many cases, information needs to be selected, prioritized and positively labeled to be put into action. Thus, a single exposure is often not sufficient to lead to change of knowledge or behaviors. Complex contagion represents spread of items under the influences of intensive, repeated and valued contacts. The assumptions of complex contagion are consistent with a number of theories. For instance, the Diffusion of Innovation Theory proposes that uptake of information occurs in most individuals by informal, personal contacts rather than through formal education [15].

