**Figure 1 F1:**
[figure not shown]
Hypothesized relations.

For patients we also expect network characteristics to be important for and related to self-management (that is, health behaviors for diet, physical activity, and smoking). Firstly, the presence of a high number of individuals with favorable self-management as previous research showed that self-management behaviors (e.g. smoking, alcohol use, obesity) are clustered within networks [12-14]. Secondly, the effect of having individuals with appropriate self-management within ones network should be more profound when these individuals are also connected to each other, with resulting opportunities for multiple social influence mechanisms [24]. Thirdly, networks which contain few individuals with depressive symptoms may be positively related to self-management, as depression has shown to have both a contagious pattern in networks [25] and to be related to worse health behaviors [26,27] and impaired efforts for achieving lifestyle change [20]. Fourthly, the presence of persons who can provide information on CVRM in patients’ informal networks (e.g. nurses or physicians) adds to the social capital of an individual and can be expected to enhance self-management [28].

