#### Hypotheses on patients

Patients are more likely to have favorable self-management and reach CVRM targets if they have social networks which contain: a high number of individuals with adequate self-management, a high number of individuals with adequate self-management who are connected to each other, few individuals with depressive symptoms, and individuals who provide access to individuals who can provide information on CVRM, particularly health professionals (such as nurses or physicians).

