**Personal characteristics** For assessment of personal characteristics of patients we will measure patient activation (*Patient Activation Measure, PAM*[38]), therapy adherence (*Medication Adherence Measure*[39]), quality of life (*EQ-5D*[40]), and depressive symptoms (*Patient Health Questionnaire, PHQ-9*[37]). Alters of patients will complete the PHQ-9. Higher total scores on these measures will indicate higher patient activation, therapy adherence, quality of life, and depressive symptoms respectively.

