### Statistical analyses

Response rates for health professionals and patients will be determined. For patients we will compare response rates between the patient group invited by either a single option for participation and the group that will be offered the choice to participate by either a telephone interview or a paper-based test in order to assess which method is most feasible for including them in social network research using *X*^2^ tests.

Reliability of reported social network connections will be investigated by examining the proportion of all possible connections that will be mutually reported present or absent (reciprocity coefficients in non-directed networks). In accordance with guidelines on handling missing values, we will substitute these by values as provided by responses of other individuals. In case of no information on connections, we will indicate no contact by a filling in a zero in the data [41].

For describing social networks of health professionals and patients we will compute network parameters and provide visualization by using graphic displays. Random permutation tests will be used for comparisons of network characteristics.

For testing our hypotheses and further explorative analyses, controlling for potential confounders, we will use multivariate logistic regression models to investigate the effect of social networks characteristics on professional performance of practice nurses and patients’ self-management and health outcomes.

In the analysis of professional performance of practice nurses regression models will include six network characteristics (density, frequency of contact, homogeneity, presence of informal opinion leaders and CVRM-coordinators, and centrality) as predictors of main interest. As control variables we will include trial arm (intervention vs control group), personal characteristics (amongst others education, years of experience in profession), and practice characteristics (practice size, involvement in other projects or organizations).

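### The test of depressive symptoms in the patient's network adjusts for the patient's own depressive symptoms, which block part of the path the protocol gives for that hypothesis

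*Protocol article*

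**What the plan says.** The section Hypotheses on patients expects better self-management and more CVRM targets reached when the network contains "few individuals with depressive symptoms, and individuals who provide access to individuals who can provide information on CVRM". The reason for the part on depression is in the Theoretical background, in the paragraph on patients after Figure 1: "depression has shown to have both a contagious pattern in networks [25] and to be related to worse health behaviors [26,27". The same sentence adds that depression hampers attempts to change lifestyle.

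The Statistical analyses section announces the general approach: "controlling for potential confounders, we will use multivariate logistic regression models to investigate the effect of social networks characteristics". For patients it plans separate models for physical activity, diet, smoking, SBP, cholesterol and risk score. The four network predictors include "number of alters with depressive symptoms, and number of alters who can provide CVRM-related information". All these models are controlled for trial arm, patient group and "several personal characteristics: age, sex, ethnicity, marital status, SES, patient activation, therapy adherence, and depressive symptoms". The follow-up models are described as similar, with the baseline outcome added. The section describes no patient model without the patient's own depressive symptoms, and no mediation analysis.

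**The concern.** The rationale for this predictor is a chain of two links. Depression passes from alters to the patient, and the patient's depression then goes with worse health behaviour. The patient's own depressive symptoms are the middle of that chain, yet the analysis lists them among the variables to be held constant as potential confounders.

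Among patients with the same depressive symptoms, whatever the alters contributed to those symptoms is no longer visible. The coefficient then answers whether depressed alters matter beyond the patient's own depression, which is narrower than the stated hypothesis. If it came out null, a reader could conclude that depression in the network is unimportant when the protocol's own mechanism was operating. The Discussion section wants the results to clarify the role of patients' social environment and to inform interventions, so that misreading would matter.

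**Working it through.** **No figure in the plan to reproduce.** The only sample size derived for this study, 338 patients, concerns the response-rate comparison (50% v 65%) and does not bear on this point.

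**Reading the sections side by side.** Let X be depression among alters, M the patient's own depressive symptoms and Y adequate self-management.

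- Theoretical background: X → M (contagion) and M → Y (worse behaviour).
- Hypotheses on patients: an overall link from X to Y, with no condition on M.
- Statistical analyses: Y regressed on X, M and the other covariates.

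The coefficient of X given M therefore excludes the path X → M → Y.

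**Approximate size.** Let a be the effect of X on M, b the log odds ratio of M on Y, and d the direct log odds ratio of X on Y. The total log odds ratio is roughly d + ab, and adjusting for M leaves d, so

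share removed ≈ ab / (d + ab).

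The protocol gives no value for a, b or d. All values below are assumptions: a from 0.1 to 0.5, b of −0.3 or −0.6, and d of −0.2 or 0. Logistic models were fitted to 400,000 simulated patients per setting, with X and the residual of M standard normal.

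With a direct effect, d = −0.2:

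| a | b | share by formula | OR without M | OR with M | share removed, simulated |
|---|---|---|---|---|---|
| 0.1 | −0.3 | 0.03/0.23 = 13% | 0.80 | 0.82 | 11% |
| 0.1 | −0.6 | 0.06/0.26 = 23% | 0.78 | 0.82 | 16% |
| 0.3 | −0.3 | 0.09/0.29 = 31% | 0.75 | 0.82 | 29% |
| 0.3 | −0.6 | 0.18/0.38 = 47% | 0.70 | 0.81 | 42% |
| 0.5 | −0.3 | 0.15/0.35 = 43% | 0.71 | 0.82 | 42% |
| 0.5 | −0.6 | 0.30/0.50 = 60% | 0.63 | 0.82 | 56% |

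The simulated shares are a little below the formula because leaving a strong covariate out of a logistic model pulls the remaining odds ratio slightly towards 1.

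With no direct effect (d = 0) the formula gives 100%. The simulation agrees within its error: for a = 0.5 and b = −0.6, the OR is 0.75 without M and 0.99 with it.

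**Chance of detection, and the reverse arrow.** Assumed setting: 500 patients, mean 0.5 depressed alters each, b = −0.6, two-sided 5% test, 1,000 runs.

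| Truth assumed | Without M: OR (detected) | With M: OR (detected) |
|---|---|---|
| Mediator, a = 0.5 per alter, no direct effect | 0.75 (58%) | 1.00 (4%) |
| Mediator, a = 0.2 per alter, no direct effect | 0.89 (13%) | 1.00 (5%) |
| Mediator, a = 0.2 per alter, d = −0.2 | 0.74 (62%) | 0.82 (29%) |
| Confounder only: M raises the number of depressed alters (log rate 0.5 per SD), no network effect | 0.78 (51%) | 1.00 (6%) |

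The first and last rows look nearly the same although the truths are opposite. Neither model alone can show which one holds.

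**The case against.** The strongest objection is that the patient's depression may be a genuine confounder. The Theoretical background lists "imitation of successful behaviours, role modelling, social comparison and selection of contacts can be drivers of contagion". Selection of contacts is among these, and patients themselves name their alters, so a depressed patient may end up with a more depressed network. In that case the planned adjustment is right and omitting it creates a false association, as the last row of the table shows. This stands, and it is why the model without the covariate should not simply replace the planned one.

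The protocol also says only that networks with few depressed members may favour self-management. It does not claim that the patient's own depression is the sole route, so a direct effect is not excluded. This stands as well.

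A reader might go further and infer that the adjustment removes the hypothesised network effects in general, with patient activation and therapy adherence as further mediators. The document does not support that. The other three network predictors rest on clustering of behaviours, social influence among connected alters, and access to information, and none is said to run through the patient's depression. Activation and adherence are introduced as background variables ("For assessment of personal characteristics of patients we will measure patient activation"), and nothing in the text places them between network and outcome; Figure 1 could not be checked. Adherence is not part of self-management as the protocol defines it, which covers diet, physical activity and smoking.

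Finally, the study is exploratory. That lowers the stakes, but it does not remove the mismatch between a stated hypothesis and the only model described for it.

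**Conclusion.** The point holds for one of the four patient network predictors, the number of alters with depressive symptoms. The planned coefficient is at most a direct effect and omits whatever part of the hypothesised effect runs through the patient's own depression. This conclusion rests on the protocol's own rationale and covariate list and needs no outside theory.

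The size cannot be fixed from the document. Under the assumed path strengths the loss runs from 11% to 56% of the log odds ratio when a direct effect exists. It is essentially complete only under full mediation, which the protocol does not assert. Saying flatly that the effect is adjusted away would therefore be too strong. Since the same covariate may also confound, the defect is that a single adjusted model is the only one described for this hypothesis, not that the covariate appears at all.

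**What to change.** For the hypothesis on alters with depressive symptoms, prespecify two models for each patient outcome, identical except that one contains the patient's own depressive symptoms and the other does not. Report the two coefficients side by side. Label the model without the covariate as the total association, open to confounding by selection of contacts, and the model with it as the direct association. State that a null adjusted coefficient alone will not be read as evidence against the hypothesis.

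In the follow-up models, use the baseline value of the patient's depressive symptoms, since a follow-up value could itself be a result of the network over the six months. Patient activation and therapy adherence may stay as covariates.

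The cost is one extra set of fits on data already being collected: six outcomes at baseline and six at follow-up, plus six more if the ordinal change models carry the same covariates, so at most 18. The drawback is that the model without the covariate may be partly confounded, which is why both are shown.
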